### Objective 2 (Evaluate differences between PASS and TAU in changing parenting practices, improving family empowerment in seeking services, and improving caregiver perceptions of team-based care)

MMRM using an ITT approach will be the general analytical approach for testing Objective 2. The analytic model for examining Objective 2 will examine intervention effects across three time points (baseline, post-treatment, follow-up). We will test for significance using a *p* value of 0.025 to be consistent across analyses.

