#### Parenting practices

The *Parent–Child Relationship Questionnaire* (PCRQ) [51] will assess parent perceptions of their parenting practices. The Negative/Ineffective Discipline factor and four items from the Positive Involvement factor will be administered. This measure has been shown to be internally consistent and sensitive to the effects of behavioral intervention [41, 52].

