Most of the outcome domains examined under Objective 1 include two measures. For example, there are two primary outcome measures – parent report of homework problems and parent report of behavior problems. In addition, ADHD symptoms will be assessed by parent report of inattention and hyperactivity-impulsivity symptoms. Because each domain generally will be assessed using two measures, tests of significance within each outcome domain will be examined using an adjusted *p* value. We have elected to use the conservative Bonferroni approach, and therefore will use a p value of 0.05/2 = 0.025. As indicated, analyses of measures completed by teachers will be underpowered. We will conduct these analyses using a* p* value of 0.05, but the primary focus will be on evaluating the magnitude of the effect size.

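### The two primary outcomes are tested by single-step Bonferroni at 0.025 each; Holm would keep the same 5% error control and give more power

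*Protocol article*

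**What the plan says.** The multiplicity rule stands in the protocol article's analysis plan for Objective 1. It sets the family at the level of the domain: "tests of significance within each outcome domain will be examined using an adjusted" p value. The reason for the divisor is that domains usually come in pairs: "Because each domain generally will be assessed using two measures". The leading example is the primary pair: "there are two primary outcome measures – parent report of homework problems and parent report of behavior problems". The procedure follows: "We have elected to use the conservative Bonferroni approach, and therefore will use a p value of 0.05/2 = 0.025". Teacher-report measures are outside this rule; they are tested at 0.05 with the emphasis on effect size.

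The analysis plan for Objective 2 adopts the same threshold, a "value of 0.025 to be consistent across analyses", and gives no separate derivation. Under the Parenting practices heading, the measure for that domain has two parts: "The Negative/Ineffective Discipline factor and four items from the Positive Involvement factor will be administered". Empowerment, team-based care and the parent form of the parent-teacher relationship subscale have one score each.

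**The concern.** Single-step Bonferroni holds both tests of a pair at 0.025 whatever the other one shows. Once one hypothesis of a pair has been rejected at 0.025, only one is left that could be falsely rejected, and testing it at 0.05 keeps the error rate over the pair at 5%. Holm uses this; the plan does not.

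The result at stake is a specific one: one primary outcome has p below 0.025 and the other has p between 0.025 and 0.05. The plan would declare only the first significant; Holm would declare both. The section on measures for Objective 1 calls homework performance and behaviour compliance a major focus of the intervention, so a claim on each is of interest, and power for the second one is given up without any return in error control.

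**Working it through.** **The plan's own figure.** 0.05/2 = 0.025. This reproduces exactly.

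**Why Holm is never worse for a pair.** Order the p values. Reject the smaller if it is below 0.025; if so, reject the larger if it is below 0.05.

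- Everything that Bonferroni rejects, Holm rejects.
- Both null hypotheses true: a false rejection needs the smaller p below 0.025, so the error is at most 2 × 0.025 = 0.05.
- One null hypothesis true: it can be rejected only if its own p is below 0.05, so the error is at most 0.05.

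This holds for any correlation between the outcomes and any valid test, including the planned mixed model.

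**Where the gain comes from.** Let x be the probability that one given outcome has p between 0.025 and 0.05 while the other has p below 0.025. With equal effects on the two outcomes, Holm adds x to the power for each outcome, 2x to the power for both, and nothing to the power for at least one.

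**Illustration A: low end of the expected effect range.** Inputs:

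- 0.35 SD: lower end of the expected range in the Sample size section, taken for both outcomes.
- 120 per arm: 240 evaluable participants / 2, same section.
- Baseline correlation 0.3: that section's autocorrelation, used here for a single baseline-adjusted comparison.
- Correlation between the two outcomes: not in the protocol; assumed 0.3, with 0 and 0.5 as a range.

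Noncentrality = 0.35 × √(120/2) / √(1 − 0.3²) = 0.35 × 7.746 / 0.954 = 2.84.

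Power at two-sided 0.025 = Φ(2.842 − 2.241) = 0.726. Power at two-sided 0.05 = Φ(2.842 − 1.960) = 0.811.

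With independent outcomes, x = (0.811 − 0.726) × 0.726 = 0.062. For correlated outcomes x comes from the bivariate normal distribution.

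| Outcome correlation | x | Per outcome: Bonferroni → Holm | Both: Bonferroni → Holm |
|---|---|---|---|
| 0 | 0.062 | 0.726 → 0.788 | 0.527 → 0.651 |
| 0.3 | 0.056 | 0.726 → 0.782 | 0.563 → 0.675 |
| 0.5 | 0.052 | 0.726 → 0.778 | 0.589 → 0.692 |

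Check for 0.3: 0.726 + 0.056 = 0.782 and 0.563 + 2 × 0.056 = 0.675.

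**Illustration B: start from 85% per measure.** The Sample size section states 85% power at 0.30 SD but no significance level. Here 85% at two-sided 0.025 is assumed. Noncentrality = 2.241 + 1.036 = 3.278; power at 0.05 = Φ(3.278 − 1.960) = 0.906. With independent outcomes, x = (0.906 − 0.850) × 0.850 = 0.048. Simulated results:

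| Outcome correlation | Per outcome: Bonferroni → Holm | Both: Bonferroni → Holm | At least one (either method) |
|---|---|---|---|
| 0 | 0.850 → 0.898 | 0.722 → 0.817 | 0.978 |
| 0.3 | 0.850 → 0.893 | 0.742 → 0.827 | 0.958 |
| 0.5 | 0.851 → 0.890 | 0.758 → 0.837 | 0.943 |

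With both null hypotheses true, simulated family-wise error was 0.046 to 0.050, identical for the two methods.

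**The level in Objective 2, on the protocol's own rule.** Parenting practices has two scores: at most 2 × 0.025 = 0.05. Empowerment, team-based care and the parent-form relationship subscale have one score each: 0.025. No domain exceeds 5%.

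**The case against.** The best defence is that Bonferroni is valid, was chosen openly and is described as conservative. Nothing in the protocol is wrong, and nothing requires success on both primary outcomes, so the gain in power for both concerns a criterion that the trial does not set. Power to show at least one effect is the same. Bonferroni also has matching simultaneous confidence intervals, and the Objective 1 analysis promises intervals for the between-group difference. Finally, the size of the gain rests on inputs outside the protocol: the correlation between the outcomes, and a single adjusted comparison in place of the planned repeated-measures model.

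All of this stands as a limit on the point. It does not remove it. Power for each primary outcome also rises, which matters without any rule about both. The direction of the gain does not depend on the assumed inputs; only its size does. And being conservative brings no benefit here, since the error bound is the same 5% under Holm.

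A reader might infer something stronger: that 0.025, derived for pairs, leaves Objective 2 with inflated error because it tests three to five scores. The upper bound over the whole objective would indeed be 3 × 0.025 = 0.075 to 5 × 0.025 = 0.125. But the protocol sets its family within each domain and nowhere claims 5% across an objective. On that rule every Objective 2 domain stays at or below 5%. Consistency is a thin reason for the level, but the level itself does no harm.

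**Conclusion.** The point holds as a minor improvement in efficiency. Single-step Bonferroni on the primary pair is valid but dominated: Holm has the same inputs and the same strong 5% control and is at least as powerful in every case. At 0.35 SD on both outcomes, with 120 per arm, baseline adjustment and an outcome correlation of 0.3, the gain is about 73% to 78% per outcome and about 56% to 68% for both. Starting from 85% per measure, it is about 85% to 89–90% per outcome and 72–76% to 82–84% for both. These figures rest on equal effects on the two outcomes and assumed correlations; if only one outcome responds, the gain is small. The documents do not support a finding of inflated error in Objective 2.

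**What to change.** Replace the fixed 0.025 by Holm within each domain that has two measures under the 0.025 rule, and first of all for the primary pair: compare the smaller of the two p values with 0.025; if it is significant, compare the other with 0.05; otherwise stop. The same sentence can serve the other two-measure domains of Objective 1 and the two parenting scores of Objective 2. Make the change before any between-group outcome results are seen.

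The cost is wording only: no change to sample size, data collection or models. The one drawback is in reporting. Simultaneous intervals that match Holm are less simple, and a 97.5% Bonferroni interval can include zero for an outcome that Holm declares significant. The plan should therefore say which intervals will be shown beside the Holm-adjusted p values, and that significance is judged by the latter. If the statistical analysis plan, which is not shown, already specifies a step-down procedure, the protocol text need only be aligned with it.

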#### Objective 3 (Explore whether changes in parenting practices, family empowerment, and perceptions of team-based care mediate the effect of intervention on child outcomes)

We will examine whether changes in parenting practices, family empowerment, or perceptions of team-based care mediate the effect of treatment (PASS, TAU) on child outcomes. We will employ the method proposed by Hayes for examining mediation effects with regression modeling approaches, utilizing PROCESS macro [64]. The models will reflect change scores in the mediators. To produce a precise estimate of mediation effects and properly account for the potential of regression to the mean, baseline measurement of the mediator will be included as a covariate [64]. In each analysis, we assess mediation by first estimating the effect of the intervention condition (PASS, TAU) on the child outcome at post-treatment, while controlling for the influence of the mediator and estimating the direct effect of the intervention on child outcomes without the mediator. The mediation effect is the difference in estimated intervention effects between the models. If the difference is not equal to zero, then there is evidence of mediation of the intervention on child outcomes.

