#### Treatment as usual (TAU)

The control condition (TAU) includes access to existing integrated behavioral health service in primary care. Services provided to families in primary care during the 16-week intervention period are highly variable. The lag time from referral to first appointment and the availability of follow-up appointments after first visit vary markedly across practices. TAU does not include support from a Community Health Partner. Both conditions will include ongoing pediatric health care informed by AAP guidelines for managing ADHD [19] and facilitated by electronic practice supports, which have been successfully incorporated into the EHR to guide PCPs in implementing ADHD guidelines. Families assigned to TAU may be referred for community-based behavioral health services during the study period.

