#### Data collection and management

Data collection strategies were designed in partnership with caregiver, educator, and clinician partners. The strategies will be reviewed and modified throughout the study to maximize participant engagement in data collection and minimize missing data. Baseline data will be collected from parents and children at the time of consent, and baseline data will be collected from teachers shortly thereafter. Mid-treatment data (specifically the ODD items from the Vanderbilt scale and the Inattention/Task Avoidance items of the Homework Problem Checklist) will be collected from parents approximately 8 weeks after baseline, and post-treatment data will be collected from parents and teachers 16 weeks after baseline. Follow-up data will be collected from parents and teachers 32 weeks after baseline. Study data will be collected and managed using REDCap tools hosted at our institution [61, 62].

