## A priori plans for data analysis for each objective

### Objective 1 (Evaluate differences between PASS and TAU in improving service utilization and child health outcomes)

To evaluate changes in service utilization, we will examine between-group changes in the proportion of children receiving mental health services (i.e., outpatient mental health therapy, school mental health services and special education services, and psychotropic medication) from pre-treatment to post-treatment to follow-up using the McNemar test. To evaluate the effect of intervention on child outcomes, a mixed effects model with repeated measures (MMRM) will be the general analytical approach employed. The model will examine intervention effects across four time points (baseline, mid-treatment [parent report of homework performance and behavior compliance only], post-treatment, follow-up). Data for all participants randomized to treatment condition will be included in the analytic model, consistent with an intent-to-treat (ITT) approach. Mixed effects models will estimate within-subject effects by time and between-treatment effects, as well as the interaction of time by treatment. A significant time by treatment interaction will indicate that one treatment is superior to the other. MMRM will include the fixed categorical effects of treatment, time, randomization stratification factor (medication status and primary care practice), and treatment-by-time interaction as well as covariates as indicated. Within-participant error variance–covariance will be assumed to be an unstructured matrix. Point estimates and confidence intervals for the mean change in outcomes for each treatment group as well as the difference in the estimated mean change between groups will be calculated.

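### The Objective 3 mediation model names the baseline mediator as its only covariate; leaving out the baseline child outcome biases the indirect effect if baseline severity also predicts change in the mediator

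*Protocol article*

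**What the plan says.** The Objective 3 analysis section of the protocol article fixes three features of the mediation model.

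- The mediator enters as change: "The models will reflect change scores in the mediators".
- The child outcome enters as a level at week 16: the analysis begins by "estimating the effect of the intervention condition (PASS, TAU) on the child outcome at post-treatment".
- One covariate is named, with precision and regression to the mean as the reasons: "baseline measurement of the mediator will be included as a covariate".

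The estimand follows: "The mediation effect is the difference in estimated intervention effects between the models". The reading rule is: "If the difference is not equal to zero, then there is evidence of mediation of the intervention on child outcomes".

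The sensitivity analyses for Objective 3 (structural equation model with several mediators, Sobel test, bootstrap) change the estimator and the test. They name no further baseline covariate.

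The other child-outcome models do bring in the baseline. Objective 1 treats baseline as one of its time points, and "MMRM will include the fixed categorical effects of treatment, time, randomization stratification factor (medication status and primary care practice". Objective 4 takes change from baseline as its outcome. The baseline values exist: "Baseline data will be collected from parents and children at the time of consent". The Sample size section labels the mediation analysis exploratory.

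**The concern.** Treatment is randomised and the mediator is not. Baseline oppositional behaviour or homework problems will predict the week-16 score of the same scale. If they also predict how discipline, empowerment or perceived team-based care change over the 16 weeks, they confound the mediator-to-outcome slope. Adjusting for the baseline mediator removes only the part of baseline severity that the baseline mediator carries.

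The plan expects PASS to move the care processes by 0.35 to 0.60 SD. A biased slope multiplied by a real effect on the mediator becomes an indirect effect that is not there. A bootstrap interval does not help, because it is an interval around the biased quantity. At stake is the reading of Objective 3 as an account of how PASS works.

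**Working it through.** **The plan's own figure.** Objective 3 has no power figure. The 85% at 0.30 SD belongs to Objectives 1 and 2. One reading reproduces it: the mean of 3 measures with AR(1) correlation 0.3 has variance (3 + 4×0.3 + 2×0.09)/9 = 0.487. With 120 per arm, SE = √(2×0.487/120) = 0.090, and at two-sided alpha 0.025 the power is Φ(0.30/0.090 − 2.241) ≈ 0.86. The article gives neither the number of measures nor the alpha behind its figure, and nothing below depends on it.

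**Model.** In SD units, with no true mediator effect on the outcome:

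- Mediator at week 16: M1 = m·M0 + g·Y0 + a·T + error
- Child outcome at week 16: Y1 = r·Y0 + 0.35·T + error

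**Inputs from the article.** r = 0.3 (Sample size); 240 evaluable families; effects within the expected range of 0.35 to 0.60 SD.

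**Assumed inputs.** Path g from baseline child score to later mediator, 0.1 to 0.3; baseline mediator-outcome correlation ρ; mediator autoregression m. Set A: ρ = 0.3, m = 0.5, a = 0.35. Set B: ρ = 0.4, m = 0.3, a = 0.45.

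**Closed form.** With the same covariates in both regressions, the difference in treatment coefficients equals a × b, where b is the slope on mediator change. Given T and M0, the remaining variation in the mediator is g(Y0 − ρM0) plus error of variance v = 1 − (m² + g² + 2mgρ). Hence the expected slope, whose true value is 0, is

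b = r·g·(1 − ρ²) / [g²(1 − ρ²) + v].

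Example, set B with g = 0.2: v = 1 − (0.09 + 0.04 + 0.048) = 0.822. Then b = 0.3×0.2×0.84 / (0.04×0.84 + 0.822) = 0.0504/0.8556 = 0.0589. The spurious indirect effect is 0.45 × 0.0589 = 0.027, and its share of the total is 0.027/0.35 = 7.6%.

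**Results at r = 0.3.** Shares are from the closed form. False positives are from 3,000 simulated trials per row, requiring both paths to be significant at 0.05.

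| Set | g | Spurious share | False positives, model as stated | With baseline outcome added |
|---|---|---|---|---|
| A | 0 | 0% | 4.0% | 4.2% |
| A | 0.1 | 3.8% | 7.5% | 5.3% |
| A | 0.2 | 8.0% | 16.4% | 4.4% |
| A | 0.3 | 12.6% | 30.5% | 4.5% |
| B | 0.1 | 3.7% | 6.9% | 5.1% |
| B | 0.2 | 7.6% | 13.4% | 4.4% |
| B | 0.3 | 11.8% | 24.4% | 4.4% |

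Across separate simulation runs, including runs using a simulated interval for the product, the range is about 3 to 13% for the share and 6 to 32% for false positives. With the baseline outcome added, the mean indirect effect is about zero.

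**Sensitivity.**

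- *Stronger persistence of the child outcome (assumed).* At r = 0.5, set A gives shares of 6 to 21% and false positives of about 11 to 70%. At r = 0.6, set B gives 7 to 24% and about 12 to 74%.
- *Small or negative path.* At r = 0.3, set A with g = 0.05 gives a share of about 2% and 5.3% false positives. With g = −0.1 the share is −3.5%.
- *No treatment effect on the mediator.* The mean indirect effect is zero, and false positives were at most 3.7% (r = 0.6).
- *Precision when g = 0.* Residual variance falls from 1 − (0.3×0.3)² = 0.992 to 1 − 0.3² = 0.91 in set A, about 8%.
- *Stratum confounding alone (g = 0, r = 0.6, a = 0.45).* An assumed shift of 0.3 or 0.5 SD in both mediator and outcome gives an indirect effect of 0.011 (6.4% false positives) or 0.029 (15.4%). Adding the baseline outcome alone does not remove it (6.9% and 19.7%); adding the stratum as well does (4.8% and 4.7%).

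**The case against.** **The article is silent, not exclusive.** It does not say that the baseline mediator is the only covariate, and a full covariate list for an exploratory analysis can sit in an analysis plan that is not shown. For the stratification factors this stands: a reader might infer that practice and medication status are left out, but the section only fails to mention them. For the baseline outcome it stands only in part. The section does deal with covariates, names one with its reasons, and fixes the outcome as a raw post-treatment level, whereas Objectives 1 and 4 bring the baseline in explicitly.

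**The size rests on a path that the article does not give.** This stands. Near zero the bias is negligible, and a negative path would hide mediation instead of creating it. The largest false-positive rates need a path of 0.3 together with more persistence than the plan's 0.3.

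**The practice argument is indirect.** The article says that under TAU "the availability of follow-up appointments after first visit vary markedly across practices". It does not say that practice shifts both the parent-rated mediators and the child scores. No passage makes medication status a confounder of this path.

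**Little hangs on it.** Objective 3 is exploratory, and no primary or secondary treatment comparison, power figure or error rate depends on it. This limits the weight of the point. It does not remove the bias when the path is non-zero.

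**Conclusion.** The point holds in conditional form. As stated, the mediation model omits a baseline variable that the trial already collects, and its indirect effect is biased if baseline child severity predicts change in the mediator given its baseline and PASS moves the mediator. At the plan's autocorrelation of 0.3, with an assumed path of 0.1 to 0.3 and no true mediation, about 3 to 13% of the effect is spuriously mediated and false positives are about 6 to 32%. Adding the baseline outcome brings these to about 0 and 4 to 5%. With a path of zero there is no bias and the gain is precision only.

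A reader might go further and conclude that the indirect effect is biased as a matter of fact, or that this omission alone rules out reading it as the mechanism of PASS. The article does not support that: it gives no estimate of the path. Nor would the repair license a mechanistic reading, since unmeasured mediator-outcome confounding would remain. The stratification factors are a secondary matter of consistency with Objective 1, with a smaller expected effect.

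**What to change.** In the Objective 3 analysis section, state that both the mediator regression and the outcome regression include the baseline value of the same child outcome alongside the baseline mediator. Carry the same term into the multiple-mediator model under the Objective 3 sensitivity analyses. For consistency with the Objective 1 model, also include practice and baseline medication status. When reporting, say that the analysis is exploratory and that unmeasured mediator-outcome confounding is not excluded.

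The cost is about one sentence in each section. Parent and child baselines are collected at consent and the stratification factors are known at randomisation, so no new data are needed for parent- and child-reported outcomes. The baseline outcome uses one degree of freedom, medication status one and seven practices six, eight in all against 240 expected families.

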#### Objective 4 (Examining Heterogeneity of Treatment Effects; HTE)

Our general strategy is to determine whether the effect of treatment on outcomes varies as a function of baseline level of family resources, caregiver health literacy and stress, child medication status, and child mental health symptom severity at baseline, following the recommendations of Wang and Ware [65]. We will use a regression modeling approach with the outcome being change from baseline to post-treatment/follow-up, treatment groups being the independent variable, a subgrouping variable or covariate being the moderator tested, and the test of moderation being the interaction of treatment by the covariate. A significant interaction term indicates that treatment varies as a function of subgroup. For a subgroup variable with more than two levels (e.g., caregiver stress), the presence of a significant treatment by subgroup variable interaction will be followed by a series of post hoc analyses to conduct pairwise group comparisons. The *p* values for post hoc analyses will be used to calculate Bonferroni adjusted *p* values and false discovery rates (FDR) resulting from multiple comparisons [66, 67]. Given that HTE analyses will likely be underpowered, a consideration of Bonferroni adjusted values and FDR in the discussion of the heterogeneity of treatment effects will be informative.

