## Plan for Sensitivity Analyses to Determine Impact of Key Assumptions

### Objective 1 and objective 2

As a sensitivity analysis, we will use a Generalized Estimating Equation (GEE) approach to analyze Objectives 1 and 2. Like MMRM, GEE is based on regression techniques and uses all data obtained from each participant. Potential advantages of GEE are that it is suitable for both continuous and dichotomous outcomes, and it does not require the correct specification of the variance–covariance structure. Additionally, GEE can be used to model data with nested structures by accounting for the correlation among outcomes for individuals in the same aggregate.

#### Objective 3

We will explore a multiple mediator model using structural equation modelling. The multiple mediator model posits a path model for each additional mediator and estimates a separate effect for each mediator. The significance of the mediation effects can be tested using a Sobel test based on an asymptotic approximation to the distribution of the indirect mediation effects [68, 69]. However, because this test is sensitive to sample size, as an alternative sensitivity analysis for mediation analyses, we also plan to use a non-parametric bootstrapping approach. Additional methods based on simulations will also be considered [70, 71].

#### Objective 4

A simultaneous assessment of mediator–moderator effects will be examined. We will examine mediated-moderation effects and moderated-mediation effects using strategies outlined by Fairchild and MacKinnon [72] and Hayes [73]. These strategies extend the mediator and multiple mediator models described under Objective 3 by adding a moderator effect and an interaction between treatment by moderator effect to the main models. Tests of significance for the individual moderator, mediator and interaction effects can be conducted using tests of joint significance and similar bootstrapping methods as for mediation effects.

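### The main mediation rule in Objective 3 has no interval, test or alpha, and its models name the baseline mediator but not the baseline child outcome, which can bias the mediated effect

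*Protocol article*

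**What the plan says.** All of this is in the protocol article.

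- **Effect measure and rule (Objective 3).** "The mediation effect is the difference in estimated intervention effects between the models". The next sentence is the rule: "If the difference is not equal to zero, then there is evidence of mediation of the intervention on child outcomes".
- **Mediator scale (Objective 3).** "The models will reflect change scores in the mediators", and "baseline measurement of the mediator will be included as a covariate" to allow for regression to the mean.
- **Outcome scale (Objective 3).** The quantity estimated is the "effect of the intervention condition (PASS, TAU) on the child outcome at post-treatment", which is a level and not a change. The baseline child outcome is not mentioned.
- **Labels (Objective 3).** The first model controls for the mediator. The second is described as "estimating the direct effect of the intervention on child outcomes without the mediator".
- **Inference (sensitivity analyses, Objective 3).** A Sobel test is offered for the multiple-mediator model, and "as an alternative sensitivity analysis for mediation analyses, we also plan to use a non-parametric bootstrapping approach".
- **Contrast.** Objectives 1 and 2 state a p value of 0.025, and Objective 1 models baseline as a time point. Objective 4 has the "outcome being change from baseline to post-treatment/follow-up", so the baseline outcome enters there.
- **Status (Sample size).** Mediation is called exploratory.

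**The concern.** There are three separate problems.

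1. **The criterion.** A difference between two estimated coefficients always carries sampling error. The population statement that mediation means a non-zero difference is sound, but Objective 3 does not say how an estimate is to be judged against zero. The tools that could do this are placed with the sensitivity analyses, so the main analysis has no decision rule that could be applied as written.

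2. **The covariates.** Randomisation protects the effect of treatment on the mediator and on the outcome. It does not protect the path from mediator to outcome. Suppose children with worse behaviour at entry have caregivers whose parenting scores change differently, and these children also score worse at 16 weeks. The mediator coefficient then picks up baseline severity. Parents report both primary outcomes and the three mediators named in Objective 3, so correlated baselines are plausible. A significance test or bootstrap does not cure this, because it would put an interval around a biased quantity.

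3. **The labels.** The effect estimated without the mediator is the total effect. The direct effect is the one estimated with the mediator in the model.

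At stake is the explanatory claim that parenting, empowerment or team-based care accounts for part of the PASS effect. The treatment comparisons of Objectives 1 and 2 are not touched.

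**Working it through.** Objective 3 states no power, alpha or sample size of its own, so there is no figure of the plan to reproduce. The check asks how often a mediator with no effect on the outcome would be declared a mediator.

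**Inputs from the protocol (Sample size)**
- N = 240 evaluable, taken as 120 per arm.
- Treatment effect on care processes 0.35 to 0.60 SD; 0.4 is used.
- Autocorrelation 0.3, taken as the outcome stability *s* from baseline to 16 weeks. That reading is an assumption.

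**Assumed, because the protocol does not give them**
- Baseline mediator-outcome correlation 0.4.
- Mediator carry-over 0.5, residual SD 0.75.
- Effect *g* of the baseline outcome on the later mediator, given the baseline mediator: 0 to 0.3.

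**Model with no true mediator effect**
- M1 = 0.5·M0 + g·Y0 − 0.4·T + 0.75·e
- Y1 = s·Y0 + √(1 − s²)·e′

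With M0 in the regression, using M1 − M0 instead of M1 leaves the mediator coefficient unchanged.

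**Spurious coefficient when Y0 is omitted**
- Variance of Y0 given M0: 1 − 0.4² = 0.84.
- Variance of the mediator given M0 and T: V = 0.84·g² + 0.75².
- Spurious mediator coefficient: b* = 0.84·g·s / V.
- Spurious mediated effect, in absolute size: 0.4·b*.

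For g = 0.3 and s = 0.3:
- V = 0.84 × 0.09 + 0.5625 = 0.6381.
- b* = 0.84 × 0.3 × 0.3 / 0.6381 = 0.0756 / 0.6381 = 0.118.
- Mediated effect: 0.4 × 0.118 = 0.047 SD.
- Residual outcome variance: 1 − 0.16 × 0.09 − 0.1185² × 0.6381 = 0.977.
- SE(b*) = √(0.977 / (240 × 0.6381)) = 0.080, so z = 1.48 and the rejection probability is 0.317.
- Treatment-to-mediator path: SE = √(4 × 0.6381 / 240) = 0.103, z = 3.88, power 0.973.
- Both significant: 0.317 × 0.973 = 0.31.

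**All settings at s = 0.3** (joint significance, nominal 5%; simulation with 3,000 replicates)

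| g | b* | Spurious mediated effect (SD) | False mediation, formula | False mediation, simulated |
|---|---|---|---|---|
| 0 | 0 | 0 | 4.9% | 5.3% |
| 0.1 | 0.044 | 0.018 | 8.0% | 8.0% |
| 0.2 | 0.085 | 0.034 | 17.2% | 17.3% |
| 0.3 | 0.118 | 0.047 | 30.8% | 30.2% |

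If outcome stability is 0.5 instead, the simulated rates for g = 0.1, 0.2 and 0.3 are 13%, 39% and 68%, with spurious effects of about 0.03 to 0.08 SD.

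**With Y0 added.** In this model the rate returns to about 5%. That is built in, because Y0 is the only confounder. In a second set of simulations (2,000 replicates), correlated stable traits of mediator and outcome were measured with error, and treatment moved the mediator by 0.35 or 0.60 SD. False mediation, judged by a Monte Carlo 95% interval for the indirect effect, was 15% to 70% without Y0 and 9% to 27% with it.

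**If treatment does not move the mediator**, the mean spurious difference is zero and the false-positive rate is at most about 5%.

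**The case against.** The strongest reply is that inference is planned. The sensitivity section names Sobel, bootstrap and simulation-based methods for mediation, and joint-significance tests for the combined mediator-moderator models. A reader might infer from Objective 3 that any non-zero estimate will be reported as mediation. Read as a whole, the article does not support that: the sentence is better taken as a definition of mediation with the test left out. What stands is that the main analysis is given no criterion, and the tests sit with the sensitivity analyses.

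Second, the covariate sentence does not say that nothing else will be adjusted for, and a full covariate list is often left to the analysis plan. That is fair. But the article chose to name the covariate and give its reason, and it took the outcome as a level. As stated, the child's baseline score enters nowhere.

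Third, a reader might infer that omitting the baseline outcome necessarily creates spurious mediation. It does not; both conditions in the working must hold. The path from baseline outcome to mediator is an assumption, and it is less evident for empowerment and team-based care than for parenting. The spurious effect at stability 0.3 is 0.02 to 0.05 SD, small beside the expected 0.35 to 0.60 SD.

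Fourth, a reader might want the 32-week outcome as the main lagged model, because mediator change and outcome appear to be taken at the same visit. The documents do not make the 16-week choice an error. PASS stops at 16 weeks and both arms then have access to integrated services, which may dilute the contrast. A lag also leaves the mediator unrandomised.

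Finally, the analysis is exploratory. That lowers the stakes but does not supply the missing criterion.

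**Conclusion.** The point holds in a limited form. Objective 3's main rule lacks an inferential criterion, and one of its two effects is mislabelled; both follow from the text alone. The named covariate set can bias the mediated effect. Under the assumptions listed above, false evidence of mediation is roughly 8% to 30% against a nominal 5% at stability 0.3, and there is no inflation if the baseline outcome does not predict the later mediator. These rates depend on correlations that the protocol does not report, so they show what is possible and are not a forecast. The primary and secondary treatment comparisons are unaffected. The change is worth making because it is nearly free and because the planned bootstrap alone would not remove the bias.

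**What to change.** In Objective 3:

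1. Include the baseline child outcome, the baseline mediator and the stratification factors (medication status and practice) in both the mediator and the outcome equation.
2. Replace the non-zero rule with a stated criterion: the bootstrap 95% confidence interval for the indirect effect excludes zero. Move the bootstrap from the sensitivity section to the main analysis.
3. Call the effect without the mediator the total effect, and the effect with the mediator the direct effect.
4. Say that adjustment reduces confounding of the mediator-outcome path but may not remove it, and report the results as exploratory, in line with the Sample size section.

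The cost is a few sentences. Baseline parent and child measures are already collected at consent, the bootstrap is already planned, and no visit or measure is added.
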